#### Outcomes for the economic evaluation

Health and social care use by residents will be recorded using specifically designed data collection forms/diaries. Data will be collected at 4, 8 and 16 months from randomisation. Contemporaneous study records (of salaries and travel expenses) will be kept to determine resource use in implementing the intervention. We will collect the bulk of resource use data from care home records but will test the accuracy of this method by comparing the results with those from a subset of individual resident care records and with centralised records of events, such as hospitalisation from the Health and Social Care Information Centre (HSCIC).

Unit financial costs for health and social care resources will be obtained from national sources (Personal Social Services Research (PSSRU) Unit Costs of Health and Social Care, British National Formulary (BNF) and NHS reference cost databases) and used to determine costs. Utility (HRQoL) values will be determined from either EQ5D-3 L, SCR QoL or DEMQOL-P-4D.

#### Interviews

We will investigate opportunities and barriers to sustainability for Stop Delirium! and its integration into routine practice through qualitative interviews with key staff. Focus groups will take place at the start and end of the intervention period. Two groups will comprise either nursing or care staff from across all intervention homes. Individual interviews with a manager and a Delirium Champion from each intervention home will take place 16 months from randomisation.

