### Aims and objectives

The primary hypothesis for the main trial will be that Stop Delirium! is a cost-effective way to prevent delirium episodes in residents of older people’s care homes. The secondary hypothesis will be that this will lead to a reduction in admissions to hospital from this population. The main objective of this pilot trial is to gather process, management, resource and scientific data to inform the design of a definitive trial. The principle objectives of this pilot and the corresponding research questions are outlined in Table 1.

**Table 1 T1:** Principle objectives, research questions and outcomes

**Principle objectives**	**Research questions**	**Outcomes**
**Process:** To provide an estimate for the number of care homes needed for the main trial	What are the potential recruitment and attrition rates for enrolment of residents?	
**Resources:** To investigate the acceptability of the proposed measurements to residents and the most appropriate informant	Which type of data collection diaries (care home resident level), designed by the team to capture health and social care resource use, are most acceptable to residents and staff (>75% completed)? And are these diaries valid (contain information that can be used to calculate costs)?	Activities of daily living Number of falls during previous 6 months
		Mortality during previous 6 months
		Hospital admissions during previous 6 months including total length of stay; number of admissions; time to first admission
		Health-related quality of life
	Which health-related quality of life measure, the EuroQol (EQ-5D 3 L) [23], ASCOT Social Care-Related Quality of Life (SCRQoL) [24] or the DEMQOL-V4 [25] is more acceptable to residents (greater % of questionnaires completed)? And are resident and proxy reports of HRQoL comparable?	
	Are baseline and outcomes measures outcome rates adequate (achieving >75% complete data for each)? And what resources are required in determining these outcomes?	
**Management:** To assess the adherence to, and sustainability of Stop Delirium!	What are the adherence rates for the various components of the intervention? And what are the facilitators and barriers for sustainability and integration into routine care, after the intervention?	Total number of medications Health related quality of life Health and social care costs as measured by health related quality of life measures and health and social care resource use

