### Intervention

#### Stop Delirium!

Intervention homes will receive the Stop Delirium! package. This is a multicomponent intervention designed to prevent delirium in care home residents, based on the best delirium prevention and practice change evidence. It aims to modify key resident and environmental delirium risk factors (pain, infections, dehydration, poor nutrition, constipation, polypharmacy, sensory impairment, limited mobility and sleep disturbance) by improving the quality of care. A specialist delirium practitioner (DP) leads a delirium prevention educational process such that care home staff feel empowered, develop relevant skills and are able to identify opportunities for delirium prevention through the development of local care pathways and solutions tailored to the home environment. Key components (tested and refined in our previous feasibility study [22]) include:

1. Three 20-minute small group interactive education sessions for all staff in the home delivered by the DP and then offered monthly to new staff.

2. Monthly Staff Working Groups facilitated by the DP to identify key priority areas for delirium prevention in the home. Participants are drawn from staff volunteers attending education sessions.

3. A Delirium Box containing educational and implementation materials is established in each home by the home manager, supplemented by bespoke materials produced by staff members of the care home Working Groups.

4. The identification of delirium champions by the DP, who are then trained to deliver the education sessions and to facilitate Staff Working Groups under supervision, with a view to sustaining the intervention.

5. A manualised intervention to provide a consistent educational experience and approach to developing the workshops. Specific features of the intervention can be found on the European Delirium Association website [29].

The intervention will be in place for 16 months. This is 6 months longer than was allowed for in the previous feasibility phase. This period is intended to provide sufficient time for any change in practice to embed and have an effect.

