### Post-intervention assessments

Researchers, blind to allocation, will collect data 16 months from randomisation - deemed to be the start of the intervention - through administering tests on alternate days (except Sundays) for a period of one month and examining individual care home and hospital records. Researchers will record;

1. Presence of delirium on any day during a 1-month post-intervention period. Screening will use the 6-CIT and short version CAM. Presence or absence of delirium for those positive will be confirmed using the DRS-R-98 (as at study baseline). Ratings for a 10% subsample will be compared to determine inter-rater reliability.

2. Delirium severity (proportion of residents with DRS-R-98 severity scale score >15.25 at any assessment) during the 1-month post-intervention period.

3. Delirium duration (days positive for delirium) during the 1-month post-intervention period.

4. Number of medications.

5. Activity of Daily Living (ADL) scores.

6. Falls during previous 6 months.

7. Mortality during previous 6 months.

8. Hospital admissions during previous 6 month including;

a. total length of stay

b. number of admissions

c. time to first admission

The 6-CIT is a dementia screening tool used in primary care. The short CAM is a four-question instrument used extensively for delirium screening and diagnosis [26]. The DRS-R-98 is a valid measure of delirium occurrence and severity [27]. We know that the training of the researcher affects performance of these instruments [34]. Researchers will be trained before both the baseline and post-intervention assessments. As part of the analysis, we will also check inter-rater reliability at baseline by comparing ratings for a 10% subsample.

If a resident scores positive on the short CAM, indicating a possible delirium, subject to prior consent, the care home manager will be informed in writing on the day of assessment so that appropriate action can be taken. A copy of this letter will be held on file with the consent forms.

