#### Treatment data

*Intervention compliance.* Adherence to the components of the intervention at 4, 8 and 16 months from randomisation - early middle and late phases of delivery - will be recorded using a standardised *pro-forma*. Data recorded will include degree of completion for each component (education sessions, working groups) and reasons for noncompliance, allowing calculation of adherence rates for each, and identification of components that may need alteration before use in a definitive trial.

*Concomitant interventions.* Any new initiatives or projects introduced during the study period by other agents (researchers, health organisations or local authorities-especially those aimed at reducing hospital admissions and falls - will be recorded at 4, 8 and 16 months from randomisation).

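### The pilot asks about sustainability after the intervention, but every planned contact with staff falls no later than month 16, when delivery ends

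*Protocol article*

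**What the plan says.** The Management objective in Table 1 (Aims and objectives) is "To assess the adherence to, and sustainability of Stop Delirium". Its research question has two parts: the adherence rates for the components, and "what are the facilitators and barriers for sustainability and integration into routine care, after the intervention".

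The dates are fixed in four places:

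- **Length of the intervention** (Stop Delirium!): "The intervention will be in place for 16 months".
- **Start of the clock** (Post-intervention assessments): researchers "will collect data 16 months from randomisation - deemed to be the start of the intervention". Month 0 is therefore randomisation.
- **Adherence** (Treatment data): recorded "at 4, 8 and 16 months from randomisation - early middle and late phases of delivery".
- **Staff contacts** (Interviews): focus groups at the start and the end of the intervention period, and "Individual interviews with a manager and a Delirium Champion from each intervention home will take place 16 months from randomisation".

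The Stop Delirium! section adds that champions are trained during delivery to run the education sessions and the working groups under supervision, so that the intervention can continue afterwards. The Analysis section says that the qualitative data will be used to understand what helps or hinders sustainability and integration over time.

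**The concern.** The question concerns a period that the schedule does not reach. Sustainability here depends on a hand-over: champions take on tasks that the delirium practitioner has led or supervised. Whether the sessions and working groups continue, and what gets in their way, can be seen only after that support has stopped. On the stated dates, nobody asks staff about that period and no record of staff practice covers it.

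The risk lies in how the result is reported. High adherence at month 16, together with favourable interviews on that date, could be presented as showing that the intervention is sustainable. The adherence figure would describe supported delivery, and the interviews would be a forecast for the time after it. The Discussion expects the definitive trial to use an intervention period of between 10 and 16 months, so its designers have reason to want to know what lasts after delivery.

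**Working it through.** The check is a timeline. The plan states no figure for follow-up of staff practice, so there is none to reproduce.

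**End of delivery.** Start + duration = 0 + 16 = month 16.

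**Time observed after delivery.** Last planned time point − month 16:

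| Source | Planned time points (months) | Last − 16 |
|---|---|---|
| Adherence record | 4, 8, 16 | 0 |
| Focus groups | 0, 16 (start and end of the period) | 0 |
| Manager and champion interviews | 16 | 0 |

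The article itself calls the month-16 adherence record the late phase of delivery, so that record belongs to the intervention and not to the time after it.

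**Is there any later source?** The only collection that runs past month 16 is the one-month outcome period: alternate-day delirium assessments and a review of care home and hospital records. The items listed there are resident outcomes such as delirium, medications, activities of daily living, falls, deaths and admissions. None shows whether staff keep up the sessions or working groups.

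**Room to move the interviews.** Delivery plus the outcome period takes 16 + 1 = 17 months. The Design section gives 24 months in all, so at most 24 − 17 = 7 months remain. The article does not break the 24 months down, and each home is randomised only after its own baseline work. As an assumption, let a home be randomised *r* months into the study. The time left after its outcome period is then 24 − (*r* + 17) = 7 − *r*:

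- *r* = 0: 7 months
- *r* = 3: 4 months
- *r* = 7: none

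Any months reserved for analysis and reporting reduce these figures further.

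**The case against.** The strongest reply is that the question is qualitative. It asks for facilitators and barriers, and the article promises neither a rate of sustained adherence nor a verdict that the intervention is sustainable. Champions work under supervision during delivery, so managers and champions interviewed at month 16 can report obstacles to hand-over that they have actually met. Focus groups at both ends plus closing interviews are a reasonable way for a pilot to find such factors. All of this stands. It narrows the gap to the time after support is withdrawn. It does not close the gap, because Table 1 names that time and the objective is to assess sustainability.

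A second reply is that adherence to delivery is properly measured during delivery. That is also right: having no adherence record after month 16 is not a fault in the adherence measure. The fault would be to read that measure as evidence of sustainability.

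A third reply is that the 24 months may have no slack and that an interview one month after delivery says little. The first part cannot be settled from the article, and it is why the fix has a fallback. The second is a reason to hold the interviews as late as possible.

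Three stronger readings are tempting, and the article does not support them:

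- **That the trial can report only what staff expect.** This ignores experience gained during delivery and supervised hand-over.
- **That the adherence form omits who ran each session, so that hand-over goes unseen.** The form is not shown, and the article's list of what it will include is not exhaustive.
- **That this result decides whether the definitive trial relies on champions.** No section says so, and the changes anticipated in the Discussion concern intervention length, recruitment timing and the screening method.

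**Conclusion.** The point holds as a mismatch between a stated question and stated dates. There are 0 months of planned observation of staff practice after delivery ends, so for that period the trial can report only anticipated sustainability. For the 16 months of delivery, including supervised hand-over, it can report experience.

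This rests on two assumptions: that the practitioner's support stops when the 16-month intervention does, and that month 16 is a nominal date on which interviews are actually held. A delay of a few weeks would not change the conclusion.

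The weight is moderate. One part of a principal objective cannot be answered as worded. The primary outcome, the intraclass coefficient, the confidence interval for the difference in delirium rates and the sample-size inputs are untouched.

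**What to change.** Hold the same manager and champion interviews after the one-month outcome period, as late as the 24-month timetable allows, and ask then whether the education sessions and working groups have continued. Report the interval between the end of delivery and each interview, since it may differ between homes.

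The cost is a change of date and one added topic, with no extra interviews. There are two downsides. Some managers or champions may have left by then, although this turnover is itself informative. The slack in the timetable is not stated, and later-randomised homes will have less of it.

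If the interviews cannot be moved, or have already taken place in a home, restate the objective and limit the conclusion to anticipated sustainability at the end of delivery. This costs only wording. In either case, report month-16 adherence as adherence in the late phase of delivery and do not present it as evidence of sustainability.

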### Analysis

In this pilot trial, quantitative analysis will focus on descriptive statistics and will focus on confidence interval estimation rather than formal hypothesis testing. An intention-to-treat-analysis of clinical data will be undertaken blind to allocation. Any statistical analysis in a definitive trial would include multilevel modelling to account for the cluster design. Qualitative data from interviews and focus groups will be analysed combining a grounded theory (constant comparison) approach and narrative analysis to develop understanding of the factors (such as contextual, leadership, and organisational structures and knowledge, beliefs and behaviours of staff) that facilitate or inhibit sustainability of the intervention and its integration into routine practice over time.

#### Baseline assessments

A preliminary analysis consisting of a series of descriptive tables summarising baseline characteristics of a) the 14 care homes and b) residents in the study will be presented. Summary and comparison statistics will be used to describe and compare the intervention and control arms. The baseline delirium prevalence (residents positive for delirium/total number of residents screened) will be determined from the baseline data.

#### Outcome assessments

The delirium occurrence rate for intervention and for control arms will be calculated (number of residents with an episode of delirium in one month/total number of residents screened). A 95% confidence interval for the difference in rates will be constructed. Intraclass coefficients will be calculated for delirium occurrence using data from the post-intervention period. Summary statistics and comparisons between the intervention and control arms post-intervention will also be calculated for all primary and secondary outcomes as detailed previously. Recruitment and attrition will be summarised, together with rates of consent, consultee consent, withdrawals and deaths. In addition, Kaplan-Meier survival curves will be constructed for the following outcomes:

1. Time to first hospital admission in previous 6 months.

2. Mortality in previous 6 months.

Outcomes for hospital admission and mortality are assessed starting 10 months after randomisation. This is because we hypothesise that the intervention will not be able to influence outcomes before that time as it provides education for staff, which they need to operationalise into actions that will then affect residents. We have not therefore collected data for events occurring between randomisation and 10 months for hospital admission. We will have information on deaths and will present a summary of these data for the intervention and the control homes.

Data from the first and second stages of resident recruitment will be analysed together with a separate sensitivity analysis to investigate the impact of the later phase.

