## Methods/Design

### Design

We plan a pilot cluster, randomised, controlled trial conducted in 14 care homes for older people over 24 months, an embedded health economic feasibility study, and individual and focus group interviews to investigate sustainability and integration of the intervention.

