### Randomisation

Homes will be randomised on a 1:1 basis to receive either active intervention (Stop Delirium!) or control (usual care) by the Leeds Clinical Trials Research Unit (CTRU), stratified by care home size (<20 or under, ≥20 residents) and the percentage of residents with dementia (<62%, ≥62%). Randomisation will take place only after the baseline recruitment and assessment of residents have been completed for each home.

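### As written, the pilot's 95% confidence interval for the difference in delirium rates makes no allowance for the 14 randomised homes, and it will be too narrow if the ICC is above zero

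*Protocol article*

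**What the plan says.** The Design section describes the trial: "We plan a pilot cluster, randomised, controlled trial conducted in 14 care homes for older people over 24 months". Under Randomisation, homes are allocated 1:1, which gives 7 per arm if the split is exact.

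The Analysis section says that the quantitative work "will focus on confidence interval estimation rather than formal hypothesis testing". Its only statement on handling clusters concerns a different study: "Any statistical analysis in a definitive trial would include multilevel modelling to account for the cluster design".

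Under Outcome assessments, the occurrence rate in each arm is the "number of residents with an episode of delirium in one month/total number of residents screened". The next sentence is: "A 95% confidence interval for the difference in rates will be constructed". No interval method is named. The section adds: "Intraclass coefficients will be calculated for delirium occurrence using data from the post-intervention period". It does not say that this coefficient will be used in the interval.

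The Sample size section explains the design effect and why it is needed, but only for sizing a cluster trial.

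**The concern.** The rates are resident counts pooled over homes, and the interval is placed on their difference. A statistician following these sentences would compute an ordinary two-proportion interval that treats residents as independent. The independent units are the 14 homes, so between-home variance belongs in the standard error and only about 12 degrees of freedom (14 − 2) are available to estimate it.

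Forgoing hypothesis tests does not remove the problem, because a confidence interval rests on the same standard error as a test. The point matters for this pilot because interval estimation is its stated focus, delirium occurrence is its primary outcome, and Table 1 lists the comparison of rates between intervention and control homes as a research question. The Sample size section also says that no care-home data exist on which to base an effect size. This interval would be such data, and readers would take from it more precision than 14 homes can supply.

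**Working it through.** **Inputs from the article.** 14 homes, 1:1 allocation (Design, Randomisation). Control rate 14% and a one-third reduction, so 14% × 2/3 = 9.33% (Sample size).

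**Assumed, because the article gives neither.** m = 10 to 20 residents analysed per home, equal across homes; ICC = 0.02 to 0.10.

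**The plan's own figure.** The article gives no figure for the interval. Its 809 per group (individually randomised, 80% power, 5%) reproduces with a two-sided, continuity-corrected two-proportion formula at 14% v 9.4%: 766 before correction, then 766/4 × [1 + √(1 + 4/(766 × 0.046))]² = 809. At exactly 9.33% the same formula gives 784. The rates used here are therefore in line with the article's own.

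**Formulas.**
- Unadjusted half-width = 1.96 × SE, with SE = √[p₁(1−p₁)/n + p₂(1−p₂)/n] and n = 7m.
- Design effect DE = 1 + (m − 1) × ICC.
- Adjusted half-width = t(0.975, 12 df) × SE × √DE, with t = 2.179.
- Ratio of widths = √DE × 2.179/1.96. This does not depend on the rates.
- Coverage of the unadjusted interval ≈ 2Φ(1.96/√DE) − 1.

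**Worked example, m = 15, ICC = 0.05.** n = 105 per arm. SE = √[(0.1204 + 0.0846)/105] = 0.0442. Unadjusted: 1.96 × 0.0442 = 8.7 points. DE = 1 + 14 × 0.05 = 1.70. Adjusted: 2.179 × 0.0442 × √1.70 = 12.6 points. The ratio is 1.45. Around a difference of 4.7 points, the interval runs from about −4 to 13 points unadjusted and about −8 to 17 adjusted.

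**Range.** Simulated coverage is from a beta-binomial model with 7 homes per arm and 40,000 runs per setting.

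| m | ICC | DE | Half-width, unadjusted → adjusted (points) | Ratio | Unadjusted coverage: formula / simulated |
|---|---|---|---|---|---|
| 10 | 0.02 | 1.18 | 10.6 → 12.8 | 1.21 | 92.9% / 92.6% |
| 10 | 0.05 | 1.45 | 10.6 → 14.2 | 1.34 | 89.6% / 89.4% |
| 10 | 0.10 | 1.90 | 10.6 → 16.3 | 1.53 | 84.5% / 83.9% |
| 15 | 0.02 | 1.28 | 8.7 → 10.9 | 1.26 | 91.7% / 91.7% |
| 15 | 0.05 | 1.70 | 8.7 → 12.6 | 1.45 | 86.7% / 86.5% |
| 15 | 0.10 | 2.40 | 8.7 → 14.9 | 1.72 | 79.4% / 79.0% |
| 20 | 0.02 | 1.38 | 7.5 → 9.8 | 1.31 | 90.5% / 90.2% |
| 20 | 0.05 | 1.95 | 7.5 → 11.6 | 1.55 | 84.0% / 83.5% |
| 20 | 0.10 | 2.90 | 7.5 → 14.2 | 1.89 | 75.0% / 74.7% |

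At an ICC of zero the unadjusted interval covers about 95%. At 0.01 it still covers 92.4% to 93.5% in simulation. A t-interval on home-level proportions held 95.0% to 95.4% in every setting in the table, so a simple remedy works with 14 homes.

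**The case against.** The strongest reply is that the article never says the interval is unadjusted. The ratio under Outcome assessments defines the point estimates, and a cluster-robust, design-effect or home-level interval would fit the sentence about the confidence interval. The authors plainly understand clustering: they explain the design effect and plan to estimate the ICC. An analysis plan that is not shown may name the method, which articles often leave to such a plan.

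Part of this stands. A reader might infer that an unadjusted formula has been chosen and that the interval is bound to be too narrow. The documents support neither as a fact: the method is inferred, and the shortfall needs an ICC above zero. What does not stand is that this is simple silence. The Analysis section sets out what the pilot will do and then places cluster modelling in the definitive trial. Beside an interval on pooled resident rates, that points the analyst away from adjustment.

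A second reply is that this is a pilot meant to inform design, with no decision rule tied to this interval. That is correct. It lowers the severity but does not make the standard error right.

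A reader might also want to add that the ICC should be estimated net of arm, that the stratification factors should be adjusted for, or that the printed size cut under Randomisation is garbled. The first two are details commonly left to an analysis plan. The third is a separate wording matter that has no bearing on the interval.

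**Conclusion.** Wrong as written, and it should be fixed. The text plans an interval on pooled resident rates and mentions accounting for the cluster design only for the definitive trial. Followed literally, it makes no allowance for home.

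For 10 to 20 residents per home and an ICC of 0.02 to 0.10, the interval that allows for clustering is about 1.2 to 1.9 times as wide, and the unadjusted one covers about 75% to 93%. These figures rest on an assumed ICC, assumed and equal cluster sizes, and 7 homes per arm. The half-widths in points also depend on the 14% and 9.33% rates. The 14% is a point prevalence, so one-month occurrence may differ from it, but the width ratios would not change. The shortfall is small at the low end of the range and serious at an ICC of 0.05 or more with 15 to 20 residents per home.

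It is not a fatal flaw: conduct and data are unaffected, and no progression rule in the article uses the interval.

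**What to change.** Add to Outcome assessments a statement to this effect: the difference in one-month delirium occurrence and its 95% confidence interval, and the intervals for the other between-arm comparisons, will allow for clustering by home. Suitable methods are a t-interval on home-level proportions, or a mixed or GEE model with a small-sample correction. Report the result with the ICC and its confidence interval. In the Analysis section, amend the sentence on multilevel modelling so that it no longer reads as confining allowance for clusters to the definitive trial.

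If the analysis plan already specifies such a method, a short cross-reference is enough. The change is to wording and analysis only, and should be settled before outcomes are analysed. The price is wider intervals: 12.6 rather than 8.7 points either side in the worked example.

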## Background

Delirium is a distressing but preventable condition that is common in older people. It is associated with increased morbidity, mortality, functional decline, hospitalisation, and significant healthcare costs [1,2]. Despite its high prevalence and poor outcomes, delirium has been under-researched and neglected in clinical practice [1,3]. Most research on delirium has focused on hospital patients. Another (expanding [4]) high risk group is residents of care homes for older people. The burden of delirium is likely to be considerable in residents of long-term care given the clustering of known delirium risk factors [5], especially the high prevalence of dementia. Individuals admitted to hospital from long-term care have higher rates of delirium [6], and institutional residence has been identified as a risk factor for post-operative delirium [7]. However, there have been few good-quality studies, investigating delirium in long-term care. A systematic review [8] found no studies of delirium incidence and no studies from the United Kingdom (UK). The median point prevalence of delirium was reported to be 14% in studies reflecting the UK model of long-term care [8].

We know that delirium can be prevented (reduced by one-third) in hospitals [9-11]. Successful interventions are multifaceted and rely on a combination of staff education and systematic screening for modifiable risk factors (attending to dehydration, pain, sensory impairments and poor mobility). These are areas of care that should be equally applicable to long-term care settings. It is not yet known, however, whether a similar approach might be effective in care homes. The recent National Institute for Clinical Excellence (NICE) delirium guideline recommends that such interventions should be implemented in long-term care given the likely benefits. In addition, it recommends that the clinical and cost effectiveness of these interventions should be investigated as a research priority [12].

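### The pilot's rate difference uses neither the randomisation strata nor the home as unit; a home-level interval adjusted for both strata would be sound at almost no cost (minor)

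*Protocol article*

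**What the plan says.** The Design section states: "We plan a pilot cluster, randomised, controlled trial conducted in 14 care homes for older people over 24 months". Under Randomisation, homes are allocated 1:1, stratified by size (cut at 20 residents) "and the percentage of residents with dementia" (cut at 62%). The Background explains why long-term care residents carry a heavy delirium burden, citing the clustering of risk factors, "especially the high prevalence of dementia".

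Under Outcome assessments, each arm's rate is "number of residents with an episode of delirium in one month/total number of residents screened", followed by "A 95% confidence interval for the difference in rates will be constructed". No interval method, stratum term or home term is given. The Analysis section says the pilot "will focus on confidence interval estimation rather than formal hypothesis testing", and mentions multilevel modelling only for a definitive trial. An intraclass coefficient is to be estimated from the post-intervention data, but it is not linked to the interval.

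**The concern.** The rate difference is written as a crude contrast of two pooled proportions. It leaves out two features of the design.

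- **Home as unit.** Homes were randomised, so variation between homes belongs in the standard error. An interval built from residents as if independent omits it and is too narrow.
- **Strata.** Allocation is balanced on two factors, one of which the article treats as an important risk factor. In a home-level comparison that omits them, the between-stratum variation stays in the error term although balance has largely removed it from the arm contrast. That interval is wider than it needs to be, by an amount that depends on how strongly the strata predict delirium.

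The two omissions act in opposite directions, so the interval method decides which one matters. The pilot reports intervals in place of tests, so this interval is its main comparative result and a likely input to the design of the definitive trial.

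**Working it through.** **The plan's own figure.** The article gives no figure for the width of this interval. Its one sample-size figure, 809 per group, is reproduced by 14% versus 9.4%, two-sided 5%, 80% power, with continuity correction. It does not bear on this point.

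**Inputs from the article.** 14 homes, 1:1, so 7 per arm; overall rate 14% (Sample size section).

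**Assumed, because the article does not give them.** 10 to 20 assessed residents per home (m); ICC within strata 0 to 0.10; 6 low- and 8 high-dementia homes, split 3 and 4 in each arm; delirium rates in low/high homes of 14/14%, 12/16%, 10/18% or 7/21%; size not prognostic; no intervention effect.

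**Step 1: pooled resident interval (plain reading), m = 15, ICC 0.05.**
- Half-width = 1.96 × √(2 × 0.14 × 0.86 / 105) = 0.094.
- Design effect = 1 + (15 − 1) × 0.05 = 1.70.
- Half-width needed = 0.094 × √1.70 = 0.122.
- Coverage = 2Φ(1.96/√1.70) − 1 = 2Φ(1.503) − 1 = 86.7%.

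Simulation (beta-binomial outcomes, 10/18%) gives 0.094 against 0.124 needed, with coverage 86.4%. The same formula for other settings:

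| Residents per home | ICC 0 | ICC 0.02 | ICC 0.05 | ICC 0.10 |
|---|---|---|---|---|
| 10 | 95% | 92.9% | 89.6% | 84.5% |
| 15 | 95% | 91.7% | 86.7% | 79.4% |
| 20 | 95% | 90.5% | 84.0% | 75.0% |

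In simulation, coverage stays in this range even at 7/21%. A strong dementia effect does not make the pooled interval too wide.

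**Step 2: add the strata but not the homes.** At m = 15, 10/18%, ICC 0.05, the stratified resident-level half-width is 0.093 and coverage 85.9%, slightly worse than the crude interval.

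**Step 3: home-level interval without and with the strata, m = 15, ICC 0.05, 10/18%.**
- Within-stratum variance of a home rate: mean p(1 − p) = (6 × 0.10 × 0.90 + 8 × 0.18 × 0.82)/14 = 0.1229; then 0.1229/15 × 1.70 = 0.0139.
- Between-stratum part left in the unadjusted variance: 2 × (3 × 4/7) × 0.08² / 12 = 0.0018.
- Without strata (12 df): 2.179 × √((0.0139 + 0.0018) × 2/7) = 0.146.
- With both strata (10 df): 2.228 × √(0.0139 × 2/7) = 0.141.
- Ratio about 1.04.

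Simulated mean half-widths are 0.142 and 0.137, the same ratio; the adjusted interval covers 95.5%.

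**Step 4: the other stratum effects, same formula, m = 15, ICC 0.05.**

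| Low/high rate | Without strata | With strata | Ratio |
|---|---|---|---|
| 14/14% | 0.136 | 0.139 | 0.98 |
| 12/16% | 0.139 | 0.140 | 0.99 |
| 10/18% | 0.146 | 0.141 | 1.04 |
| 7/21% | 0.163 | 0.140 | 1.16 |

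The ratio rises with larger homes and a smaller ICC. Simulated half-widths at m = 20 and ICC 0 are 0.102/0.091 = 1.12 at 10/18% and 0.124/0.091 = 1.36 at 7/21%. At m = 10 and ICC 0.05 the formula gives 1.03 and 1.12. For ICC up to 0.05, most settings lie at about 5 to 12% (10/18%) and 15 to 30% (7/21%). At 7/21% the unadjusted home-level interval covers 98.0% (m = 15, ICC 0.05).

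**Step 5: cost when the strata do not matter.** 2.228/2.179 = 1.023, so the adjusted interval is about 2% wider; simulations put it at no more than about 3%.

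**The case against.** The strongest case against has four parts.

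1. **Direction.** A reader might infer that omitting the strata makes the stated interval too wide whenever dementia share predicts delirium. The documents do not support that. The article describes a pooled-resident contrast, and Step 1 shows such an interval is too narrow at any appreciable ICC. Excess width needs a home-level interval, which the article does not state, together with a fairly strong stratum effect. At 12/16% there is no gain.
2. **Strength of the predictor.** The article names dementia as a risk factor but gives no strength for a home-level share cut at 62%. It also excludes residents whose severe dementia prevents assessment, so the whole-home share may track risk poorly among those analysed. This stands, and it is why the gain is shown as a range.
3. **Silence is not exclusion.** The article nowhere says the strata or the homes will be left out, and an analysis plan that is not shown may settle the interval method. This stands and limits the point. What remains is that the estimator the article does define is crude and resident-pooled.
4. **Consequence.** The pilot is descriptive, makes no formal test, and attaches no decision rule to this interval. This also stands.

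A reader might further infer that the dementia share will be unavailable, since the Care home data list does not name it. That does not follow: the value is needed to randomise each home, and the number of residents is on the list.

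**Conclusion.** The point holds in a limited form and is minor. The stated rate difference uses neither the strata nor the unit of randomisation. Read plainly, its interval covers about 84 to 90% at an assumed ICC of 0.05, and is close to 95% only if homes do not differ within strata. A home-level interval without the strata is valid but conservative when dementia share is fairly strongly prognostic, and otherwise loses nothing of note. A home-level interval with both strata covers about 95% in every setting tested, so the recommendation does not depend on which reading is right. The sizes rest on assumed home sizes, ICCs and stratum effects, none of which the article gives. No general claim about excess width is justified.

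**What to change.** In the Outcome assessments section, state that the difference in delirium occurrence and its 95% interval come from a regression of home-level delirium rates on arm, size stratum and dementia stratum, as used at randomisation, with a t interval on 10 degrees of freedom (14 homes less four parameters). The pooled arm rates can still be reported descriptively. Do not add the strata to a resident-level interval that ignores clustering; that makes coverage slightly worse.

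The cost is a sentence of text and two degrees of freedom: up to about 3% more width than an unadjusted home-level interval if the strata are not prognostic. The interval will also be wider than the crude pooled one (0.137 against 0.094 at 15 residents per home, 10/18%, ICC 0.05), which is the price of correct coverage. With homes of unequal size, an unweighted home-level difference averages over homes, not residents, so it need not equal the pooled difference; the text should say which is reported as the main estimate.
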